# Cancer patients’ needs assessment in primary care: study protocol for a cluster randomised controlled trial (cRCT), economic evaluation and normalisation process theory evaluation of the needs assessment tool cancer (CANAssess)

**DOI:** 10.1136/bmjopen-2021-051394

**Published:** 2022-05-04

**Keywords:** PALLIATIVE CARE, PRIMARY CARE, Adult palliative care

## Abstract

**Introduction:**

Unmet needs in patients with cancer and their carers are common but poorly identified and addressed. The Needs Assessment Tool-Cancer (NAT-C) is a structured consultation guide to identify and triage patient and carer unmet needs. The NAT-C is validated, but its effectiveness in reducing unmet patient and carer needs in primary care is unknown.

**Methods and analysis:**

Cluster randomised controlled trial with internal pilot and embedded process evaluation to test the clinical and cost effectiveness of the NAT-C in primary care for people with active cancer in reducing unmet patient and carer need, compared with usual care. We will recruit 1080 patients with active cancer (and carers if relevant) from 54 general practices in England.

Participating practices will be randomised 1:1 to either deliver an NAT-guided clinical consultation plus usual care or to usual care alone. Consenting participants with active cancer and their carers (if nominated) will be asked to complete study questionnaires at baseline, 1 and 3 months for all, 6 months except for those recruited outside of the last 3 months of recruitment, and attend an NAT-C appointment if allocated to an intervention practice. An internal pilot will assess: site and participant recruitment, intervention uptake and follow-up rates. The primary outcome, the proportion of patients with an unmet need on the Supportive Care Needs Survey Short Form 34 at 3 months postregistration, will be analysed using a multilevel logistic regression. Mixed-methods process evaluation informed by Normalisation Process Theory will use quantitative survey and interview data from clinicians and key stakeholders in cancer care to develop an implementation strategy for nationwide rollout of the NAT-C if the intervention is cost-effective.

**Ethics and dissemination:**

Ethical approval from London-Surrey REC (20/LO/0312). Results will be peer-reviewed, published and made available to research participants.

**Trial registration number:**

ISRCTN15497400.

Strengths and limitations of this studyWe are testing the clinical and cost-effectiveness of the Needs Assessment Tool-Cancer, which has been validated and shown to be acceptable to patients and clinicians during feasibility testing.Feasibility testing led to modifications of intervention delivery and informed trial design, making successful completion of the trial more likely.CANASSESS is a cluster randomised controlled trial of 54 general practices across 2 regions in England, making it likely that findings will be generalisable nationwide.By necessity, participants, health professionals delivering the intervention and study researchers will be aware of treatment allocation; potential bias will be monitored during the trial.COVID-19 presents unique challenges in terms of safely conducting clinical trials in primary care.

## Introduction

Unmet needs in people with cancer and their carers are common but poorly identified and addressed. Many people with cancer experience unmet needs across multiple domains.^1^ General Practitioners (GPs, family doctors) and other clinicians in primary care would like to do more to support their cancer patients, but there is no agreed evidence-based best approach.^2^ Difficulties are compounded by inconsistent co-ordination of care with oncology services as GPs may be unaware of problems unless patients present directly. However, people with cancer often do not attend primary care for cancer care and systematic, routine holistic assessment of patient problems is rare.^3^ In addition, patients commonly volunteer only the most pressing problem to their clinicians; open enquiry in one study only found an average of one problem presented, whereas systematic enquiry discovered an average of ten, many of which were severe and distressing.^4^

Tools are available to assist clinicians caring for people with cancer,^5^ but few are designed to identify and triage care needs in the everyday busy clinical setting and across all stages of active disease from diagnosis through to end of life care. Furthermore, although needs assessment tools are advocated,^6^ there is no rigorous research evidence to indicate whether they actually improve practice and patient outcomes. A needs assessment tool can reduce unmet needs by providing a consistent and comprehensive approach to prompting discussion patients’ range of support and care needs; helps professionals triage tailored action and is useful for audit and service planning.^7–11^ Through triage, an assessment tool may help reduce late referrals for palliative care, and improve referrals where there are physical, psychological, social and spiritual problems.^12 13^ However, tools currently available are commonly highly detailed and long for daily clinical use.^14–16^

### Development of the Needs Assessment Tool Cancer

The Needs Assessment Tool-Cancer (NAT-C) was developed in Australia, where it has been shown to reduce unmet needs of patients in oncology clinics.^3^ We adapted and validated this tool for use in UK primary care.^17^ Use of the NAT-C aims to reduce unmet supportive and palliative care needs of cancer patients and their carers by supporting systematic clinician assessment of patient and carer needs across multiple domains. Identified problems may be managed in primary care or through referral to other services.

Our phase II feasibility study found that a randomised trial is feasible in terms of recruitment, data quality and intervention delivery.^18^ Required changes to improve study processes were identified, specifically, confirmation of participant acceptability to be directed to a known NAT-C clinician. Our Resource Use Questionnaire (RUQ) was also modified following feedback from patient participants in the feasibility study. Clinicians, patients and carers also viewed the tool positively and supported need for a definitive trial. A key alteration to the NAT-C was to develop the paper-based tool into digital templates for use in standard electronic clinical record systems (EMIS, SystmOne) in accordance with clinician preferences.

### Aims

The CANAssess trial aims to evaluate the clinical effectiveness and cost effectiveness of the NAT-C in reducing unmet needs of patients and carers in primary care carer compared with usual care alone.

## Methods and analysis

### Design summary

CANAssess is a multicentre, two-arm, pragmatic, cluster randomised controlled trial (cRCT) with 12-month internal pilot, embedded process evaluation and cost-effectiveness evaluation. A cRCT design reflects that the intervention would be implemented at general practice level and reduces contamination in the control group.

The trial opened to recruitment on 1 October 2020, recruitment is expected to cease on 1 June 2022 and participant follow-up will end on 1 September 2022.

Trial objectives and outcomes are reported in box 1.

Box 1CANAssess Primary, Secondary, internal pilot, economic and process evaluation objectivesPrimary objectiveTo test the effectiveness of the Needs Assessment Tool-Cancer (NAT-C) compared with usual care in reducing unmet patient need as measured using the Supportive Care Needs Survey Short Form 34 (SCNS-SF34)^33^ at 3 months postregistration.Secondary objectivesTo evaluate the effectiveness of the NAT-C compared with usual care with regard to:Patient unmet need on psychological, health system information, physical and daily activity, patient care and support, and sexuality domains of the SCNS-SF34 at 1, 3 and 6 months.Patient performance status, measured using the Australian-modified Karnofsky Performance Status^34^ at 1, 3 and 6 months.Patient severity of symptoms, measured using the Revised Edmonton Symptom Assessment System^35^ at 1, 3 and 6 months.Patient mood and quality of life as measured by the European Organisation for Research and Treatment of Cancer Quality of Life-C15-Palliative questionnaire^14^ at 1, 3 and 6 months.Carers’ ability to care and carer well-being as measured using the Carer Experience Scale^36^ and Zarit Burden Interview-12^37^ at 1, 3 and 6 months.To evaluate intervention delivery, uptake and fidelity of the NAT-C as measured by:NAT-C training of general practitioners and nurses in each general practice.Completed NAT-C consultations by patient and general practice (including completion of individual items of the NAT-C).Length of NAT-C consultations.Referral patterns and actions taken to meet identified unmet need (including referrals to health professionals and/or services) from the completed NAT-C.Internal pilot objectivesTo assess sufficiency of numbers of general practices and patients at 12 months post start of recruitment, we will proceed with the trial unchanged if we have 80% (43) sites open and are recruiting to 80% (48 participants per month) of target. We will assess intervention uptake, follow-up rates and potential for selection bias.Health economic objectivesService utilisation, referral patterns and cost-effectiveness measured using:Bespoke Resource Use Questionnaire for capturing patient healthcare service utilisation and referral patterns at 1, 3 and 6 months.The EQ-5D-5L,^38^ ICEpop CAPability Supportive Care Measure^39^ and CES to generate quality-adjusted life-years and estimates of well-being at 1, 3 and 6 months.Process evaluation objectivesTo assess the adequacy of NAT-C training, intervention fidelity, possible mechanisms of action and issues regarding implementation in practice if the intervention is effective.

### Recruitment setting

The study aims to recruit patients and their carers from 54 general practices (clusters) from four geographical regions (recruitment ‘hubs’) in Yorkshire, East Midlands and the North East of England. Locations were selected to ensure a range of multi-ethnic, rural and urban populations to maximise generalisability of findings.

### Recruitment of general practices

Site identification and recruitment is detailed in figure 1. General practices will be eligible unless they: took part in the feasibility study, have or are planning to implement within the duration of the trial a systematic holistic cancer care intervention that overlaps with the NAT-C, or lack capacity and capability to deliver the study.

**Figure 1 F1:**
[figure not shown]
Study flow chart. CRN, Clinical Research Network; GP, general practitioner; NAT-C, Needs Assessment Tool-Cancer. Expression of Interest (EOI), Short Message Service (SMS)

### Cluster randomisation

Where practice manager agreement is obtained, capacity and capability confirmed, and initial read-code search completed, participating general practices (clusters, n=54) will be randomised sequentially via an automated system at the clinical trials research unit (CTRU). General practice randomisation will be 1:1 to: implement the NAT-C in addition to usual care, or usual care alone, using a computer-generated minimisation programme incorporating a random element to ensure arms are balanced for stratification factors:

Locality: Urban or rural area.^19 20^List size: <5000, 5000–10000, >10000.^20^A GP training practice (obtained from site feasibility questionnaire): yes, no.

General practices and research nurses providing participant recruitment and follow-up support across multiple surgeries will, by necessity, be aware of treatment allocation. However, no member of the research team will be involved with intervention delivery to minimise performance bias. A structured risk of bias assessment is presented in online supplemental file 1. Participating practices will be free to withdraw from the study without negative consequence. In the event of practice withdrawal, we will inquire about reasons for withdrawal and may recruit replacement practices.

10.1136/bmjopen-2021-051394.supp1Supplementary data

### Participant eligibility

Eligibility criteria are shown in box 2

Box 2Patient/carer inclusion/exclusionPatient inclusion criteriaAdults (aged 18 years and above).Diagnosis of active cancer (receiving anticancer treatment both with curative or palliative intent; managed with ‘watch and wait’; recurrent or metastatic; or inoperable).Willing and able to complete questionnaires at the trial follow-up schedule.Provision of written or observed verbal informed consent.Sufficient knowledge of the English language to provide informed consent and complete trial questionnaires. The use of an appropriate translator/interpreter is allowed.Patient exclusion criteriaPatients in complete remission (no clinical or radiological evidence of cancer, and at least 1-month post anticancer treatments).Patients with basal cell carcinoma.Patients living in a care home or other institutional setting.Patients within 1 month of receiving their initial cancer diagnosis.Carer inclusion criteriaAdults (aged 18 and above).Nominated by participant.Able to complete trial measures.Written or observed verbal informed consent.Sufficient knowledge of the English language to provide informed consent and complete trial questionnaires. The use of an appropriate translator/interpreter is allowed.Carer exclusion criteriaEmployed to look after the participant.

### Participant recruitment

General practices will identify eligible patients by searching cancer registers and screening for eligibility. Eligible patients will be sent a letter with a patient information sheet and expression of interest form. General practices may also send an SMS text message or amended letter to patients inviting them to express interest in the study on the CANAssess website. Patients will provide informed consent (online supplemental file 2) ahead of registration into the study. Consented patients may nominate carers for participation in the trial. Carers agreeing to participate will provide consent. The full process of participant recruitment is presented in figure 2. For any participant or carer who wishes to withdraw from the trial, we will collect a reason for withdrawal and cease data collection, but keep collected data unless otherwise requested.

10.1136/bmjopen-2021-051394.supp2Supplementary data

**Figure 2 F2:**
[figure not shown]
Participant and carer recruitment. GP, general practitioner; BCC, Basal Cell Carcinoma.

### Intervention arm (NAT-C plus usual care)

The NAT-C comprises five sections: priority referral for further assessment, patient well-being, ability of carer or family to care for patient, carer/family well-being and resulting referrals (if required). Clinicians will be encouraged to use the tool as an aide memoire, conducting a holistic patient assessment as usual, but referring to the NAT-C to ensure all domains are addressed during a consultation. The NAT-C will be completed using either the electronic medical record template (EMIS, SystmOne) or on paper. Completed paper copies of the NAT-C will be uploaded to the patient record.

At least two clinicians per practice will be trained to use the NAT-C either face to face, via webinar or online using a training package piloted during feasibility work.

Participating patients at intervention arm surgeries will be offered a 20 min appointment or home visit depending on clinical need, guided by an NAT-C trained clinician using the tool within approximately 2 weeks of study registration. Appointments will take place either at the practice, at patients’ homes or remotely via phone or video according to clinical judgement and coronavirus guidelines. Participating carers will be welcome to accompany patients to their appointment, however, the NAT-C allows assessment of carer need through patient response.

### Usual care

Usual care is defined as management normally provided for patients with cancer registered at the general practice concerned.^21^

### Data collection

Required data, assessment tools, collection time points and processes are summarised in table 1.

**Table 1 T1:** Summary of assessments*

Participant assessment (including who is involved)	Timeline (months postrandomisation)			
	Baseline	1	3	6
Eligibility and consent				
Consent (P, C, R)	X			
Eligibility (assessed by clinician, R)	X			
Background and demographics				
General demographics (P, C, R)	X			
Cancer demographics (R-case notes)	x			
Comorbidities (R-case notes)	X			
Follow-up data (collected from case notes)				
Survival status (R)	Ongoing and at the overall end of the trial			
Related unexpected serious adverse events (R)	Ongoing			
NAT-C Intervention (R)	One month post participant registration			
Usual care data (R)	X	X	X	X
Prequestionnaire (phone call at 1, 3, 6 months)				
Performance status (AKPS)	x	x	x	x
COVID status	x	x	x	x
Participant Questionnaire Booklet				
(Self-completion with researcher support if needed)				
Unmet needs (SCNS-SF34)	x	x	x	x
Symptoms (ESAS-r)	x	x	x	x
Mood and Quality of Life (EORTC QLQ-C15-PAL)	x	x	x	x
EuroQol-5 Dimension L (EQ-5D-5L)	x	x	x	x
ICECAP-SCM	x	x	x	x
Healthcare Resource Use (including usual care data and referrals)	x	x	x	x
Carer Questionnaire Booklet				
(Self-Completion with researcher support if needed)				
Carer Experience Scale	x	x	x	x
Carer well-being and burden (ZBI-12)	x	x	x	x

*P, participant; C, carer-giver; R, researcher.

AKPS, Australian-modified Karnofsky Performance Status; EORTC QLQ-C15-PAL, European Organisation for Research and Treatment of Cancer Quality of Life-C15-Palliative; EQ-5D-L, EuroQol-5 Dimension L; ICECAP-SCM, ICEpop CAPability Supportive Care Measure; NAT-C, Needs Assessment Tool-Cancer; SCNS-SF34, Supportive Care Needs Survey Short Form 34; ZBI-12, Zarit Burden Interview-12.

### Baseline assessments

Clinical data including comorbidities, cancer stage and treatments will be collected at baseline by the research nurse from the participant’s medical record. Demographic information will be collected on participants, including age, sex, participant ethnicity and living arrangements, during the researcher baseline discussion. For carers, age, sex, relationship status and living arrangements will be collected.

### Participant questionnaires

Self-reported participant and carer outcome measures will be collected via questionnaires at baseline, 1-month and 3-month postregistration. Questionnaires will also be collected at 6 months for participants and carers registered before 3 months prior to the end of participant recruitment.

Participants will be able to complete questionnaires using paper forms sent by post, online via Research Electronic Data Capture (REDCap) or with a researcher over the phone or face-to-face, as appropriate. Only CTRU data and statistical staff will have direct access to the dataset.

Researchers will telephone participants to confirm questionnaire receipt and assess and collect performance (AKPS) and COVID-19 status.

### Intervention data collection

A research nurse will collect information on NAT-C intervention delivery and content, including the timing, duration, mode of delivery, referrals and subsequent appointments from the participant’s medical record.

### Safety data collection

In this population, it is expected that episodes of acute illness, infection, new medical problems and deterioration of existing medical problems will occur and could result in prolonged hospitalisation, hospital readmission, significant or permanent disability or incapacity, or death.

Only serious adverse events fulfilling the definition of a related unexpected serious adverse event resulting from administration of any research procedure, and participant deaths during the trial period, will be recorded. Survival status of participants will be ascertained by research nurses from general practices ahead of sending study follow-up questionnaires.

### Deaths

The date and cause of all deaths occurring during the trial period (to last participants 3-month follow-up assessment) will be collected by the researcher from participant’s medical record.

## Statistical considerations

### Sample size

The study has been powered to detect improvement in patients’ level of unmet need as measured by proportion of patients reporting at least one moderate or high need in domains of the Supportive Care Needs Survey Short Form 34 (SCNS-SF34).^22^

Assuming that the proportion of patients with an unmet need on any SCNS-SF34 domain will be similar to that observed pre-intervention by Waller 2012^3^: 64%, then a sample size of 1080 patients recruited from approximately 54 general practices (540 patients, 27 practices per arm), will provide 85% power with a 5% significance level to detect a relative difference of 22% in the proportion of patients with an unmet need. This is an absolute difference of 14%, from 64% to 50%.

The sample size assumes: a 20% loss to follow-up rate by 3 months, to account for eligible patients who are, or are nearing, end of life; an intracluster correlation coefficient (ICC) of 0.05; an average general practice size of 20; and an adjustment to account for variable practice sizes of 4–40. Given heterogeneity in the design of palliative care services and availability of resources through general practices, and median ICCs reported for outcome variables (0.03) and primary care settings (0.045), an ICC of 0.05 will be used.^23^

### Internal pilot and progression criteria

The internal pilot will end 12 months from recruitment of the first general practice. Data from participants in the internal pilot will be included in the main study analysis.

Progression criteria for recruitment are shown in table 2, based on a traffic-light system of green (go), amber (review) and red (stop), and has been agreed by an independent trial steering committee (TSC) and funder. The TSC will be provided with descriptive data, presented by arm and by general practice to assess internal pilot progression criteria, adherence to the intervention and follow-up, and selection bias at approximately 12 months after the start of the recruitment to inform a decision on continuation of the trial. The internal pilot will not lead to any changes to data collection or the intervention and data from participants in the internal pilot will be included in the main study analysis.

**Table 2 T2:** Progression criteria for internal pilot

Criteria	Green (go)	Amber (review)	Red (stop)
Recruitment General practices assessed at 12 months	80% open (≥43)	50%–80% open (27-42)	<50% open (<27)
Recruitment Participants per month assessed at 12 months (target after 3 months: 60 per month)	≥80% (≥48)	50%–80% (30-47)	<50% (<30)

### Statistical analysis

There are no planned interim analyses; outcome data will be analysed once only. All analyses will be conducted on the intention-to-treat (ITT) population, in which all general practices and participants will be included in the analysis according to the group which the GP practice was randomised, and regardless of non-adherence to the intervention or withdrawal from the study. A two-sided 5% significance level will be used for statistical endpoint comparisons.

The flow of patients and general practices through the trial will be presented in a Consolidated Standards of Reporting Trials diagram.

As appropriate for cluster trials recruiting participants after randomisation,^24^ statistical testing of baseline participant data will be at the end of the internal pilot and at the end of the study to assess for selection bias.

Analyses of primary (overall unmet need) and secondary outcomes (unmet needs, severity of symptoms, quality of life, carer well-being and burden) will use multilevel logistic or linear regression (as appropriate) with participants nested within general practices, and general practices treated as a random effect. The model will be adjusted for the following fixed effects: GP practice-level stratification factors, important participant-level covariates (eg, baseline unmet need, age, sex, cancer status, baseline performance status), and other relevant known predictors of outcome. Results will be expressed as point estimates, p values, ICCs and 95% CIs.

Reasons for attrition and missing participant data will be summarised and mechanisms for missing data we explored according to participant characteristics, intervention and control groups.^25^ To conduct analysis on the ITT population, missing data will be multiply imputed at individual participant level under the missing at random assumption. Sensitivity analyses of the primary endpoint will be conducted to assess impact of missing data, choice of imputation model and missing at random assumption.

Quantitative summaries for AKPS score and corresponding change from baseline will be presented at baseline and months 1, 3 and 6 by treatment group. Intervention delivery will be summarised overall and by general practice to evaluate uptake of the NAT-C, adherence to the processes and quality of intervention delivery.

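### Performance status (AKPS) is listed as an effectiveness outcome, but the stated analysis only summarises it by arm

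*Protocol article*

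**What the plan says.** Box 1 (under Design summary) opens the secondary objectives with a comparative aim, NAT-C against usual care. Its second item is "Patient performance status, measured using the Australian-modified Karnofsky Performance Status", at 1, 3 and 6 months. The other four items under that aim are the SCNS-SF34 domains, symptom severity (ESAS-r), mood and quality of life (QLQ-C15-PAL), and the carer measures (CES and ZBI-12).

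The Statistical analysis section then says that analyses of the primary and "secondary outcomes (unmet needs, severity of symptoms, quality of life, carer well-being and burden) will use multilevel logistic or linear regression", with practice as a random effect and adjustment for stratification factors and participant covariates. For these, "Results will be expressed as point estimates, p values, ICCs and 95% CIs".

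AKPS is treated separately at the end of the section: "Quantitative summaries for AKPS score and corresponding change from baseline will be presented at baseline and months 1, 3 and 6 by treatment group". Otherwise, performance status enters the analysis only as an adjustment variable, among the "important participant-level covariates (eg, baseline unmet need, age, sex, cancer status, baseline performance status".

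**The concern.** The objective is comparative and the stated analysis is not. A table of means and mean changes by arm gives no effect estimate with an interval, so it cannot show whether the NAT-C changed performance status relative to usual care, or how precisely that is known.

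Two features of this trial make unadjusted summaries a weak basis for comparing arms:

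- General practices are the randomised units, so patients within a practice are not independent. A simple SD or SE by arm ignores this.
- Participants are recruited after their practice is randomised, and the article itself plans checks for selection bias. Change from baseline uses the baseline value crudely. It is not adjustment for baseline AKPS, the stratification factors and the other covariates.

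Readers would probably compare the AKPS columns informally. If the investigators decided only after seeing the table whether to test the difference, that test would be post hoc.

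**Working it through.** **Side-by-side comparison.** The five clinical and carer items in Box 1 are set against the outcomes named for regression in the Statistical analysis section:

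| Box 1 item | Named for multilevel regression? |
|---|---|
| SCNS-SF34 domains | Yes (unmet needs) |
| AKPS | No; summaries and change from baseline by arm |
| ESAS-r | Yes (severity of symptoms) |
| QLQ-C15-PAL | Yes (quality of life) |
| CES and ZBI-12 | Yes (carer well-being and burden) |

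AKPS is the only one of the five without a modelled comparison. It is also the only one given its own sentence with a different, descriptive treatment. The rule "A two-sided 5% significance level will be used for statistical endpoint comparisons" has no AKPS comparison to apply to.

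**Is a modelled comparison feasible?** No stated figure is in dispute. The sample size calculation is used only to obtain a plausible design effect.

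Inputs from Sample size: "a sample size of 1080 patients recruited from approximately 54 general practices (540 patients, 27 practices per arm"; 64% versus 50%; 85% power; two-sided 5%; ICC 0.05; mean practice size 20, range 4 to 40; 20% loss by 3 months.

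Assumption: the article gives no coefficient of variation (CV) for practice size. Taking SD as range/4 gives (40 − 4)/4 = 9, so CV = 9/20 = 0.45.

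1. Patients per arm under individual randomisation, without continuity correction: 223.
2. Evaluable patients per practice: m = 20 × 0.8 = 16.
3. Design effect: DE = 1 + [(CV² + 1)m − 1] × ICC = 1 + (1.2025 × 16 − 1) × 0.05 = 1 + 18.24 × 0.05 = 1.912.
4. Total to recruit: 2 × 223 × 1.912 / 0.8 = 1066, against 1080 stated. The planned figure is reproduced closely.

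Now borrow the same ICC and CV for AKPS (an assumption, since the article gives no ICC for AKPS):

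5. Evaluable per arm at 3 months: 540 × 0.8 = 432. Effective number: 432/1.912 = 226.
6. SE of the difference in SD units: √(2/226) = 0.094.
7. 95% CI half-width: 1.96 × 0.094 = 0.18 SD. Difference detectable with 80% power: (1.96 + 0.84) × 0.094 = 0.26 SD. Both are before covariate adjustment.

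**How misleading could an unclustered comparison be?** If a reader treated patients as independent, the SE would be understated by 1 − 1/√DE. With m = 16 and CV 0.45:

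| ICC for AKPS | DE | SE understated by |
|---|---|---|
| 0.01 (assumed) | 1.18 | about 8% |
| 0.03 (median outcome ICC quoted in Sample size) | 1.55 | about 20% |
| 0.05 (planning value for the primary outcome) | 1.91 | about 28% |

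This range is illustrative. The value m = 16 reflects loss by 3 months and does not carry over to month 1, or to month 6, which is not collected for participants registered in the last 3 months of recruitment.

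**The case against.** The best defence has four parts.

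- **The article is condensed.** It rests on a full protocol available on request, and any analysis plan is unseen. Saying that summaries will be presented does not say that nothing else will be done. The list of modelled outcomes is also shorthand: it omits mood and carers' ability to care, both in Box 1. This stands in part. Omission from the list alone would be weak evidence. The dedicated AKPS sentence is what fixes a descriptive treatment, and it conflicts with Box 1 whatever a later document adds.
- **Descriptive reporting of one secondary measure is legitimate.** This stands. It then has to be labelled as descriptive, which Box 1 does not do.
- **Dependence on who survived and could be assessed, and lack of blinding, affect the modelled outcomes too.** This stands. A model among survivors does not remove the dependence on survival. These problems do not single out AKPS, and the point does not rest on them.
- **Any single figure for the understated SE is an assumption.** This stands: the article gives neither a CV nor an ICC for AKPS, and no AKPS test or SE is promised.

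A reader might infer that the AKPS objective will go unanswered altogether. The article does not support that. Summaries by arm carry some descriptive information, and a model could be specified elsewhere.

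**Conclusion.** The mismatch is real and lies within the article itself: a comparative objective is paired with a non-comparative analysis. It affects one of five clinical and carer secondary items, at three time points. For that item the article states no between-arm estimate, interval, covariate adjustment or allowance for clustering. The primary endpoint, the sample size and the other secondary outcomes are unaffected, so this should be corrected but does not threaten the trial's main conclusion.

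The verdict rests on the text alone. The feasibility figures (half-width 0.18 SD, detectable difference 0.26 SD) and the 8% to 28% range depend on an assumed CV of 0.45, 16 evaluable patients per practice and a borrowed or assumed ICC. The article supports no firm figure for how misleading the AKPS summaries would be.

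**What to change.** Preferred: add AKPS to the secondary outcomes analysed by the multilevel linear model already planned, with practice as a random effect and adjustment for baseline AKPS, the stratification factors and the stated covariates. Report an adjusted mean difference with 95% CI at 1, 3 and 6 months. State that the estimate is conditional on being alive and assessed, and make that consistent with the multiple imputation planned for the intention-to-treat analysis. The summaries by arm can stay alongside.

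Alternative, if AKPS is meant to be descriptive only: reword Box 1 so that it is not listed as an effectiveness outcome.

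Either change is about one line and needs no new data. The preferred option adds one more secondary outcome to compare, a small cost in multiplicity. The choice should be made before outcome data are analysed.
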